### Timetable

The visit plan is outlined in Fig. 1. In phase I, close monitoring of the safety parameters and additional assessment of the MRI will occur.

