## Methods/design

### Study design

The NOVOCART™ Disc study is a nonconfirmatory, prospective, multicenter, unmasked, randomized study with two phases aimed at gathering preliminary clinical information on NOVOCART™ Disc plus and NOVOCART™ Disc basic used in the treatment of a herniated disc. Phase I aimed to develop a safety profile of the investigational medicinal product NOVOCART™ Disc plus. The objectives of phase II are mainly to provide a basis for a confirmatory clinical trial design and proof of concept. Twelve trial sites are planned to participate in this combined phase-I/II study; three of them have already participated in phase I. In total, 120 patients meeting the inclusion criteria will be randomized, treated according to the randomization, and followed up for 5 years. The primary study endpoint of the phase II is the difference in the Oswestry Disability Index (ODI) between treatment groups 2 years after the intervention. This index has emerged as the most commonly recommended condition-specific outcome measure for spinal disorders. It is a self-administered questionnaire divided into 10 sections designed to assess the limitations of various activities of daily living [11, 12]. The Short Form-36 (SF-36) questionnaire and EuroQuality of Life-5 Dimension (EQ-5D) are applied to assess changes in health status and quality of life [13, 14]. Moreover, changes in leg and back pain are assessed by the Visual Analog Scale (VAS) [15]. Numerical measurements in the disc height, volumetry, and signal intensity of index and adjacent discs and categorical evaluations, such as degeneration scale and the presence or absence of stenosis, are determined by magnetic resonance imaging (MRI). Neurological and functional status and the quantity of current pain medication and time to return to work after surgery are documented. The serology of HIV, hepatitis and *Treponema palladium* are determined preoperatively. Laboratory values (IL-6, Leukotriene, and CRP) as safety vales are being evaluated only in phase I of the study. Adverse events and serious adverse events are documented. Histological investigation of the explanted tissue is performed. Primary and secondary outcome parameters are outlined in more detail in Table 1.

**Table 1 Tab1:** Primary and secondary outcome parameters

Primary outcome parameter	Oswestry Disability Index (ODI), German and Austrian version, at 5 years’ follow-up to measure degenerative lumbar disc-related disability. [11, 12]

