### Randomization

Randomization is performed intraoperatively by envelope and separately for phase I and phase II of the study. In phase I, 24 patients are randomly assigned to NDplus and NDbasic in a 1:1 allocation ratio. In phase II, 96 patients are randomly assigned to NDplus, NDbasic or follow the standard of care treatment (surgery only, SC). The allocation ratio in phase II is 2:1:1. Altogether, 60 patients will be assigned to NDplus, 36 to NDbasic, and 24 to SC (Fig. 3). Two randomization schedules are generated by CROs using Rando™ (CRO’s proprietary randomization software). The randomization schedule is kept at the CRO by the randomization code administrator, who is independent from the study team. A copy of the randomization schedule is provided to TETEC AG.

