#### Safety variables

Adverse events (AEs) will be coded according to the latest Medical Dictionary for Regulatory Activities (MedDRA™) version available at the day of database closure. The analysis of adverse events will focus on treatment-emergent adverse events (TEAE). The frequency and percentage of TEAEs and possibly related TEAEs (that is, any possibly, probably, or definitely related TEAEs) will be summarized according to primary system organ class and preferred term and tabulated by treatment group. All laboratory values will be classified as normal or abnormal according to the laboratories’ normal ranges. Morphological parameters like the Modic Score, the detection of an extra discal fluid collection and re-herniation of the treated disc will be monitored by a MRI protocol. An independent data safety monitoring board (DSMB) has reviewed the phase I data, and no concerns have been raised. An ongoing evaluation by the DSMB will be undertaken during phase II. If relevant concerns should be detectable like increased reherniation rates, a discontinuation of the trial must be considered.

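### Phase I patients are monitored more closely and no surgery-only patient is in phase I, so pooled by-arm rates of silent findings partly reflect how hard each arm was looked at

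*Protocol article*

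**What the plan says.** Four statements in the protocol article bear on this.

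- **Monitoring (Timetable, repeated in the Fig. 1 caption):** "In phase I, close monitoring of the safety parameters and additional assessment of the MRI will occur".
- **Laboratory markers (Study design):** "Laboratory values (IL-6, Leukotriene, and CRP) as safety vales are being evaluated only in phase I of the study".
- **Allocation (Randomization):** "In phase I, 24 patients are randomly assigned to NDplus and NDbasic in a 1:1 allocation ratio". For phase II, "The allocation ratio in phase II is 2:1:1", in the order NDplus, NDbasic, SC. The totals are then pooled: "Altogether, 60 patients will be assigned to NDplus, 36 to NDbasic, and 24 to SC".
- **Safety reporting (Safety variables):** treatment-emergent adverse events "will be summarized according to primary system organ class and preferred term and tabulated by treatment group". The same section has Modic score, fluid outside the disc and re-herniation followed by MRI, and gives a raised re-herniation rate as an example of a concern that would put continuation of the trial in question.

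The safety section mentions neither phase nor a set of assessments common to both phases. The only separate analysis named elsewhere is by adjacent-disc status, for efficacy.

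**The concern.** A finding without symptoms is counted only if someone looks for it. Phase I patients are looked at more closely, and membership of phase I is tied to arm because SC does not exist there. Randomization cannot balance this, since it was done separately in the two phases with different sets of arms.

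A by-arm table over the pooled 60/36/24 patients therefore mixes two things: what the treatment does, and how often patients were scanned. Two contrasts are affected. Both injected arms can look worse than SC. NDbasic can also look worse than NDplus, because a larger share of it comes from phase I, and that second distortion favours the cell product.

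The findings concerned are close to the risks that the Discussion names for injecting material into a disc: extrusion, provoked herniation and inflammatory reaction. So the comparison deserves to be clean even if the distortion is modest.

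**Working it through.** **Inputs from the Randomization section.** Phase I: 24 patients at 1:1, so 12 NDplus, 12 NDbasic, 0 SC. Phase II: 96 patients at 2:1:1, so 48, 24, 24.

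**Reproducing the stated totals.** 12 + 48 = 60; 12 + 24 = 36; 0 + 24 = 24. These match the document.

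**Share of each arm under phase I monitoring.**

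| Arm | Phase I / total | Share |
|---|---|---|
| NDplus | 12/60 | 20% |
| NDbasic | 12/36 | 33.3% |
| SC | 0/24 | 0% |

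**Direction.** Let the true rate r be the same in all arms, and let a finding be detected with probability d1 under phase I monitoring and d0 under phase II monitoring. The pooled observed rate is

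r × [share × d1 + (1 − share) × d0].

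The ratio to SC is 1 + share × (d1/d0 − 1). Whenever d1 exceeds d0, the order is NDbasic > NDplus > SC, with no true difference.

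**Size, as illustration only.** The document gives no detection probabilities, so these are assumptions.

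| d0, d1 | NDplus : SC | NDbasic : SC | NDbasic : NDplus |
|---|---|---|---|
| 80%, 100% | 1 + 0.20 × 0.25 = 1.05 | 1 + 0.333 × 0.25 = 1.08 | 1.03 |
| 50%, 100% | 1 + 0.20 × 1 = 1.20 | 1 + 0.333 × 1 = 1.33 | 1.11 |

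With r = 10% and the second row, the observed rates are 6.0%, 6.7% and 5.0%.

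The same can be put in absolute terms. Suppose the extra monitoring finds something that the common schedule would miss in 5% to 20% of phase I patients (assumed). The pooled rate then rises by:

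- NDplus: 0.20 × 5% to 20% = 1.0 to 4.0 points
- NDbasic: 0.333 × 5% to 20% = 1.7 to 6.7 points
- SC: 0

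The gap between NDbasic and NDplus is 0.7 to 2.7 points. In patients, 12 × 5% to 20% is 0.6 to 2.4 per injected arm.

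**Set against chance.** At an assumed event rate of 10%, the standard error of NDplus minus NDbasic is sqrt(0.09 × (1/60 + 1/36)) = 6.3 points. For NDbasic minus SC it is sqrt(0.09 × (1/36 + 1/24)) = 7.9 points. The distortion lies inside sampling error over the range shown.

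**After a split by phase.** Within phase II every arm is observed at r × d0, and within phase I both arms at r × d1, so the schedule-related ratio is 1.00 in each.

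**Laboratory markers.** In phase I, 12 NDplus and 12 NDbasic patients are tested on the same schedule, which is a balanced comparison. SC has no patients under that testing, so no SC rate exists.

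**The case against.** **The article does not say in so many words that safety tables merge the phases.** It is a condensed account, and a full analysis plan could well present safety by phase; the first interim analysis already looks at the 24 phase I patients alone. This stands as a limit on certainty. But the rule that is printed is tabulation by treatment group, beside arm totals pooled over phases, and followed literally it gives the unequal comparison.

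**The tabulation sentence concerns adverse events, and MRI findings are in a separate sentence.** Also correct. No pooled by-arm MRI rate is spelled out, and a visit-by-visit MRI summary would keep a phase-I-only scan apart. The exposure is through MRI findings recorded as adverse events.

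**Persistent findings would show at a later common scan.** This largely stands. It confines the problem mainly to transient silent findings, and the document gives no rate for those.

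**Taking phase-I-only findings out of the comparison would drop real events from the injected arms.** This would be a fair objection to removing them. It does not apply if the overall table keeps every event and the split is shown in addition.

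**Two stronger readings are tempting, and the document does not support them.**

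- A reader might infer that laboratory-detected events can occur only in the injected arms. Study design limits only IL-6, leukotriene and CRP as safety values to phase I; it does not exclude other laboratory-detected events in phase II. CRP is also an exclusion criterion, so SC patients may have a screening value. For the three markers the SC comparison is undefined, not biased.
- A reader might infer that the unequal monitoring will set off a false re-herniation alarm at the safety board. Safety variables says that the board has already reviewed the phase I data and raised no concerns, so it has seen them for what they are.

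**Conclusion.** The point holds as a weakness in how between-arm safety rates would be presented. The imbalance in monitoring (20%, 33.3%, 0%) follows exactly from the document's own figures. The direction of any distortion follows too, if the phases are pooled and the extra assessments find anything that the common schedule misses.

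The size is not known. Fig. 1, which holds the visit plan, is not reproduced in the text available, so the number and timing of the extra scans cannot be read, and no detection rates are given. Ratios to SC of 1.05 to 1.33 and increases of 1.0 to 6.7 points illustrate the assumptions and are not estimates. The effect is probably small, in a study that calls itself nonconfirmatory and plans frequencies and percentages for adverse events. It remains worth correcting because the remedy is nearly free.

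The power figures in Table 4 are not touched: they concern the Oswestry index, and no sample size changes.

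**What to change.** Add to the Safety variables section:

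1. The overall adverse event table by treatment group stays and includes every event from both phases.
2. Between-arm safety comparisons, above all those with SC, are also presented by phase (phase II: 48/24/24; phase I: 12/12) or restricted to MRI visits scheduled in both phases.
3. Findings detected solely at a phase-I-only assessment are flagged in the listings and tables.
4. IL-6, leukotriene and CRP as safety values are reported only as NDplus versus NDbasic within phase I.

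If the full analysis plan already does this, one line in the protocol to that effect is enough.

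The cost is one extra set of tables and smaller numbers in each. At the same assumed 10% rate, confining the comparison to phase II moves the standard error of NDbasic minus SC from 7.9 to sqrt(0.09 × (1/24 + 1/24)) = 8.7 points. For NDplus minus SC it moves from sqrt(0.09 × (1/60 + 1/24)) = 7.2 to sqrt(0.09 × (1/48 + 1/24)) = 7.5 points. No event is lost.

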**Fig. 1 Fig1:**
[figure not shown]
Visit plan. In phase I, close monitoring of the safety parameters and an additional assessment of the magnetic resonance imaging (MRI) will occur

### Investigational medicinal product

NOVOCART™ Disc plus (NDisc), an autologous cell compound for ADCT, was developed to provide rehydration and maintain the biological integrity of degenerative lumbar discs to prevent secondary diseases such as recurrent lumbar disc herniation, osteochondrosis, or segmental instability. NDisc plus is an injectable, in situ-polymerizing, modified albumin, hyaluronic acid gel with ex vivo-expanded autologous disc derived chondrocyte cells as the active ingredient. NDisc plus is composed of two components: Component A is a suspension with 3.6 to 4.4 million autologous intervertebral disc cells contained in a solution of modified human albumin, human serum, culture media components, chondroitin sulfate, and hyaluronic acid. The total volume is 4 ml suspension placed in a 6 ml glass vial. Component B is a bis thio-polyethylene glycol (BTPEG) solution; the total volume is 1 ml in a 2 ml glass vial. Components A and B polymerize in situ using a dedicated application system (special dual-chamber syringe) to form the desired hydrogel. The preparation is for single use during the ADCT. The dosage is individual, and the volume of injection is, depending on the capacity of the treated disc, between 0.5 and 2 ml cell suspension volume. NDisc basic is used as the placebo in the NDisc study and is the cell-free hydrogel carrier material with an identical composition but without growth factors.

### Sequestrectomy

Surgery is performed by two trial-designated surgeons with the assistance of an operating microscope while the patient is under general endotracheal anesthesia and in a prone position. Depending on the location of the disc herniation, the spinal canal harboring the sequestrated disc material is exposed by either a minimal interlaminar fenestration or a translaminar approach [16]. In case of a lateral lumbar disc herniation, a lateral extraforaminal approach is performed [17]. Immediately after extraction, the disc tissue is transferred into a sterile transport vial and provided to TETEC AG for the GMP compliant manufacturing of the investigational medicinal product NDisc.

### Adjacent disc disease

The presents or absence of an adjacent degenerative disc is thought to be a potential factor affecting the prophylactic treatment capacity of NDisc plus. Analyses of primary and secondary efficacy variables will be performed separately for these two patient subgroups in addition to the overall analysis.

### Transplantation

Transplantation is performed 90 days after sequestrectomy. N Disc plus (NDplus) or N Disc basic (NDbasic) is applied via an injection with a dual-needle technique directly at the intended site of action. NDplus or NDbasic is to be transplanted in a comfortable lateral or abdominal position. After the treatment level is localized and local anesthesia is performed, the puncture of the intervertebral disc concerned takes place contralaterally to the disc surgery. An injection needle is placed in the center of the disc space under image guidance, and the medicinal product is injected. In case of an ADD (adjacent disc degeneration), positioning of the needles and the mandrin takes place simultaneously to minimize radiation exposure (Fig. 2).

**Fig. 2 Fig2:**
[figure not shown]
Transplantation. An injection needle is placed in the center of the disc space contra-laterally to the side of the disc surgery. In case of an adjacent disc disease, positioning of the needle takes place simultaneously to minimize radiation exposure

### Randomization

Randomization is performed intraoperatively by envelope and separately for phase I and phase II of the study. In phase I, 24 patients are randomly assigned to NDplus and NDbasic in a 1:1 allocation ratio. In phase II, 96 patients are randomly assigned to NDplus, NDbasic or follow the standard of care treatment (surgery only, SC). The allocation ratio in phase II is 2:1:1. Altogether, 60 patients will be assigned to NDplus, 36 to NDbasic, and 24 to SC (Fig. 3). Two randomization schedules are generated by CROs using Rando™ (CRO’s proprietary randomization software). The randomization schedule is kept at the CRO by the randomization code administrator, who is independent from the study team. A copy of the randomization schedule is provided to TETEC AG.

**Fig. 3 Fig3:**
[figure not shown]
Randomization. Randomization is performed separately for phase I and phase II of the study

### Sample size and power calculation

The sample size calculation is based on the primary endpoint of the study, which is the group difference in the ODI. A change of 10 units is considered as a clinically meaningful difference. Moreover, a standard deviation of 12 is assumed, based on results of a previous trial (Hägg, Fritzell, Nordwall, 2003). A sample size calculation was performed based on a two-group t-test (nQuery Advisor™ Software, version 7.0). The width of the respective confidence intervals were calculated using a large sample approximation, with 60 patients to be enrolled in the NDplus group, 36 patients in the NDbasic group, and 24 patients in the SC arm (120 patients in total). A detailed power calculation is shown in Table 4.

**Table 4 Tab4:** Power calculation

Treatment group mean / Treatment effect (contrast)	Width of two-sided 95 % confidence interval from point estimate to limit (units in standardized ODI)		Power of pairwise t-test to detect a difference in change from baseline of 10 units in ODI
	ODI sum score (SD = 12 points)	Change in ODI (SD = 14.7 points = 12*sqrt (2(1-r)) when *r* = 0.25	Change in ODI (SD = 14.7 points = 12*sqrt (2(1-r)) when *r* = 0.25
SC (*n* = 24)	4.80	5.88	–
NDbasic (*n* = 36)	3.92	4.80	–
NDplus (*n* = 60)	3.04	3.72	–
NDbasic (*n* = 36) versus SC (*n* = 24)	6.20	7.59	71 %
NDplus (*n* = 60) versus SC (*n* = 24)	5.68	6.96	79 %
NDplus (*n* = 60) versus NDbasic (*n* = 36)	4.96	6.07	89 %

### Statistical analysis

#### Efficacy variables

The analysis of efficacy variables will focus on estimation of treatment effects and differences between treatment groups. For this purpose, it is assumed that effects of treatment with SC, NDbasic, and NDplus are additive so that treatment effects can be assessed by location shifts (like mean change or median change) between treatment groups. Differences between NDbasic and SC are the total effect of NDbasic, the transplantation/implantation procedure to inject the NDbasic, and the time interval between tissue harvest and transplantation/implantation. Observed differences between NDplus and SC are the total effect of NDplus, the chondrocytes, the transplantation procedure to inject the NDplus, and the time interval between tissue harvest and cell transplantation. Consequently, observed differences between NDplus and NDbasic are assumed the sole effect of chondrocytes. All efficacy data will be presented for patients in the Full Analysis Set (FAS). Primary and secondary efficacy variables and their changes from baseline will be summarized by treatment group. An analysis of variance with factors treatment and the presence or absence of a degenerative adjacent disc (ADD/HD) will be used to evaluate continuous and quasi-continuous, approximately normal data. Confidence intervals will be based on estimated means (least square means) and the corresponding t-statistic. Additional covariates, such as baseline measurements, will be included in the model as appropriate. VAS readings will be summarized by treatment group and visit over the course of the study. MRI parameters and variables to assess functional neurological status will be summarized descriptively. Survival analysis will be used to evaluate time to return to work after surgery. The Kaplan-Meier product-limit estimator will be used to estimate the probability to return to work over time by treatment group for all patients in the FAS. Imputation of missing data has not been planned.

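### The NDplus–NDbasic contrast cannot isolate the chondrocytes: by the protocol's own description the products also differ in growth factors, and treatment is open with a self-reported primary outcome

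*Protocol article*

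**What the plan says.** Under *Statistical analysis, Efficacy variables*, the protocol article assumes additive effects and lists what each comparison contains. NDbasic versus SC contains the NDbasic material, the injection procedure and the interval between harvest and injection. NDplus versus SC contains the same kinds of item plus the chondrocytes. From this it infers that "observed differences between NDplus and NDbasic are assumed the sole effect of chondrocytes".

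Under *Investigational medicinal product*, the cells in NDplus are "contained in a solution of modified human albumin, human serum, culture media components, chondroitin sulfate, and hyaluronic acid". Of the comparator it says: "NDisc basic is used as the placebo in the NDisc study". It adds that this product "is the cell-free hydrogel carrier material with an identical composition but without growth factors".

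Under *Study design*, the trial is a "nonconfirmatory, prospective, multicenter, unmasked, randomized study". Of the ODI, the primary outcome, the same section says: "It is a self-administered questionnaire divided into 10 sections".

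**The concern.** The inference in the statistical section works only if the injected material, apart from the cells, is the same in both arms. The product section says that it is not. The list of effects also has no term for patients knowing what they received, although the trial is described as unmasked without exception and the main outcome is the patient's own report. Calling NDbasic the placebo does not help, because a placebo given openly does not equalise expectation.

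What is at stake is the conclusion rather than the estimate. The stated purpose of phase II is proof of concept and a basis for a confirmatory design, and the product section names the cells as the active ingredient. Of the three pairwise comparisons, this is the only one said to isolate them, and it has the highest stated power. Under the rule as written, any favourable difference would be credited entirely to the cells and carried into the next trial on that footing.

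**Working it through.** **1. The plan's own figures for this contrast** (*Sample size and power calculation*, Table 4). The inputs are n = 60 and n = 36, a 10-unit difference, a score SD of 12 and a correlation of 0.25. A two-sided 5% level is inferred from the 95% interval.

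- SD of change = 12 × √(2 × (1 − 0.25)) = 14.70
- SE of the difference = 14.70 × √(1/60 + 1/36) = 3.10
- Half-width = 1.96 × 3.098 = 6.07 (stated: 6.07)
- Power, noncentral t with 94 degrees of freedom and noncentrality 10/3.098 = 3.23: 89.2% (stated: 89%)

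Both figures reproduce. They describe random error in the difference between arms and say nothing about what that difference is made of.

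**2. The decomposition, completed from the other sections.** Keep the plan's additivity and write the expected outcome in each arm with these terms:

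- s: course under standard care
- h: carrier material common to both products
- p: injection procedure
- t: interval between harvest and injection
- c: chondrocytes
- g: growth factors absent from NDbasic (*Investigational medicinal product*)
- k: effect on the reported outcome of knowing one's arm (*Study design*), with a subscript for the arm

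| Arm | Expected outcome |
|---|---|
| SC | s + k_SC |
| NDbasic | s + h + p + t + k_basic |
| NDplus | s + h + p + t + c + g + k_plus |

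The contrasts are then:

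- NDbasic − SC = h + p + t + (k_basic − k_SC)
- NDplus − SC = h + p + t + c + g + (k_plus − k_SC)
- NDplus − NDbasic = c + g + (k_plus − k_basic)

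The plan's reading, that the last line equals c alone, needs both g = 0 and k_plus = k_basic. The product section speaks against the first condition. Nothing in the article supports the second.

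**3. Can another comparison recover c?** Three arms give two independent contrasts. Subtracting the first line from the second gives c + g + (k_plus − k_basic) again. No arm receives the carrier with growth factors but without cells, and no arm is masked. Phase I has only NDplus and NDbasic (*Randomization*), so it adds no new combination. The three components cannot be separated by any analysis of this design.

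**4. Size.** The article gives no type, amount or effect for the growth factors, and no figure for the effect of open treatment on the ODI. Neither g nor k_plus − k_basic can be given a value or a range from it.

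**The case against.** The strongest reply has four parts.

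*It is an assumption, openly stated, in a nonconfirmatory trial that focuses on estimation.* True, and the text should not be read as asserting a proven fact. But the protocol's own product description contradicts the assumption, and the nonconfirmatory label does not cure that when attribution is what the contrast is for.

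*The growth-factor difference rests on one clause.* This stands in part. The listed contents of NDplus include human serum and culture media components but name no growth factor; their presence is implied only by the description of NDbasic. A reader might infer that growth factors are a demonstrated second active ingredient. The documents do not support that. They show an unreconciled difference between two sections, which the sponsor can settle.

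*Open treatment is a legitimate, declared choice, and the MRI outcomes do not rest on self-report.* Both are true. The MRI analyses by the core imaging lab are less exposed to expectation, though the growth-factor question applies to them equally. The fault is not the open design but reading a purely biological effect from it on a patient-reported outcome. A reader might infer that patients should now be masked to NDplus versus NDbasic. That would be a debatable redesign in mid-trial. The 24 phase I patients, allocated 1:1, are already open, so 12 of 60 NDplus patients (20%) and 12 of 36 NDbasic patients (33%) would stay unmasked, an imbalance within the very contrast concerned.

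*The label changes no estimate, interval or sample size, and no passage makes this the primary contrast.* Correct. The comparison of NDplus as a whole product with SC, which the plan already describes as a total effect, is also untouched by the growth-factor point. What changes is what may be concluded about the cells.

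**Conclusion.** The point holds as a fault of interpretation. As described in the article, the NDplus–NDbasic difference estimates the combined effect of chondrocytes, any growth factors absent from NDbasic, and any effect of knowing the allocation. The design cannot divide it further.

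The size of the misattribution is unknown. A reader might want to express it as a share of the 10-unit difference or of the 6.07-unit half-width, but any such figure would rest on a shift that the documents do not give. It is equally possible that both extra components are small.

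The conclusion rests on two readings: that the growth-factor clause means what it says, and that unmasked includes the patients. If the sponsor shows the first to be mistaken, the growth-factor term drops out but the open-label limit on patient-reported outcomes remains.

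**What to change.** 1. Reconcile *Investigational medicinal product* with *Efficacy variables*: state whether NDplus and NDbasic differ in anything other than cells, and correct whichever section is wrong.
2. Unless the sponsor confirms that cells are the only difference, delete the sole-effect wording. Replacement text could read: *The NDplus–NDbasic difference estimates the effect of chondrocytes together with the growth factors absent from NDbasic, under open treatment.*
3. In either case, report the ODI and the other patient-reported results (pain scales, health-status and quality-of-life questionnaires) for this contrast as open-label, and limit the proof-of-concept conclusion, and what is carried into the confirmatory design, to match.

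The cost is wording only. Sample size, model, intervals and visits do not change. The downside is a slightly less favourable claim for the cells.

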**Methods/design:**

This is a multicenter, randomized, controlled, clinical phase I/II combination study. A total of 120 adult patients are allocated in a ratio of 2:1:1. Sample size and power calculations were performed to detect the minimal clinically important difference of 10 units, with an expected standard deviation of 12 in the Oswestry Disability Index, which is the primary outcome parameter. Secondary outcome parameters include the visual analog scale and the EQ-5D questionnaire. Changes in physical and mental health are evaluated using the Short Form-12 (SF-12). Moreover, radiological and functional outcomes are evaluated. The major inclusion criterion is a single lumbar disc herniation that requires sequestrectomy. Transplantation is performed 90 days thereafter. Study data generation (study sites) and data storage, processing, and statistical analysis are clearly separated.

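### Phase I patients, who could not be randomised to SC, enter both SC contrasts without a phase term in the stated ODI model

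*Protocol article*

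**What the plan says.** The Randomization section states: "Randomization is performed intraoperatively by envelope and separately for phase I and phase II of the study". For the first phase: "In phase I, 24 patients are randomly assigned to NDplus and NDbasic in a 1:1 allocation ratio". The remaining 96 patients go to three arms: "The allocation ratio in phase II is 2:1:1". The section then adds the two phases together: "Altogether, 60 patients will be assigned to NDplus, 36 to NDbasic, and 24 to SC".

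The section on sample size and power uses those totals, "with 60 patients to be enrolled in the NDplus group, 36 patients in the NDbasic group, and 24 patients in the SC arm", and Table 4 labels each contrast with them (60 vs 24, 36 vs 24, 60 vs 36).

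Under Efficacy variables the model is: "An analysis of variance with factors treatment and the presence or absence of a degenerative adjacent disc (ADD/HD) will be used". Phase is not named. Efficacy is presented for the full analysis set, with no restriction by phase. Table 5 places the primary efficacy evaluation at 24 months and covers all patients who have reached that visit. The Study design section, by contrast, attaches the primary endpoint to phase II.

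The abstract says: "A total of 120 adult patients are allocated in a ratio of 2:1:1".

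**The concern.** Phase determines which arms a patient could enter and with what probability. A patient in phase I had no chance of SC and an even chance of NDplus or NDbasic. A patient in phase II had a one-in-four chance of SC and was twice as likely to get NDplus as NDbasic. If the phases are analysed together without a phase term, treatment is partly confounded with whatever differs between them.

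The protocol itself describes such differences. Phase I came first and ran at three of the twelve planned sites, with closer safety monitoring and an additional MRI. The trial is unmasked and the ODI is completed by the patient, so a shift in the outcome between phases is possible.

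At stake is how far randomisation supports the treatment differences that the study exists to estimate. The two SC contrasts are affected most. NDplus versus NDbasic, which the protocol reads as the effect of the cells alone, is affected less.

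**Working it through.** **Inputs.** Phase I: 24 patients at 1:1, so 12/12/0 (NDplus/NDbasic/SC). Phase II: 96 patients at 2:1:1, so 48/24/24. Sum: 60/36/24, as stated. From Table 4: difference 10 ODI units, SD of change 12 × sqrt(2 × (1 - 0.25)) = 14.70. The protocol gives no alpha for the test; two-sided 0.05 is assumed, in line with the 95% intervals.

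**Step 1: reproduce Table 4.** SE = SD × sqrt(1/n1 + 1/n2), half-width = 1.96 × SE, power from the noncentral t distribution.

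| Contrast | n | Half-width (stated) | Power (stated) |
|---|---|---|---|
| NDplus-SC | 60 vs 24 | 6.96 (6.96) | 79.5% (79%) |
| NDbasic-SC | 36 vs 24 | 7.59 (7.59) | 71.9% (71%) |
| NDplus-NDbasic | 60 vs 36 | 6.07 (6.07) | 89.2% (89%) |

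The half-widths match exactly and the powers to within a point. Table 4 therefore does count the phase I patients in both SC contrasts.

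**Step 2: bias without a phase term.** Let d be the mean ODI outcome in phase I minus that in phase II, equal across arms. The share of each arm that comes from phase I is 12/60 = 0.20 for NDplus, 12/36 = 0.33 for NDbasic and 0/24 = 0 for SC. Each contrast is shifted by the difference in shares times d (taking ADD/HD as balanced across phases). The protocol gives no d, so a range is shown.

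| Contrast | Bias | d = 3 | d = 5 | d = 10 |
|---|---|---|---|---|
| NDplus-SC | 0.20d | 0.6 | 1.0 | 2.0 |
| NDbasic-SC | 0.33d | 1.0 | 1.7 | 3.3 |
| NDplus-NDbasic | (0.20 - 0.33)d = -0.13d | -0.4 | -0.7 | -1.3 |

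**Step 3: all 120 patients with a phase term.** The phase effect is estimated within NDplus and within NDbasic, because SC has no phase I patients. Its variance, in units of SD², is 1/(1/(1/12 + 1/48) + 1/(1/12 + 1/24)) = 1/(9.6 + 8.0) = 0.0568. Each contrast gains (difference in shares)² × 0.0568:

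- NDplus-SC: 1/60 + 1/24 + 0.20² × 0.0568 = 0.0606; SE = 14.70 × sqrt(0.0606) = 3.62; half-width 7.09; power 78.3%.
- NDbasic-SC: 1/36 + 1/24 + (1/3)² × 0.0568 = 0.0758; SE = 4.05; half-width 7.93; power 68.8%.
- NDplus-NDbasic: 1/60 + 1/36 + (2/15)² × 0.0568 = 0.0455; SE = 3.13; half-width 6.14; power 88.6%.

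Power uses 116 error degrees of freedom (120 patients minus four parameters; ADD/HD is left out of this calculation).

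**Step 4: SC contrasts on phase II patients only.**

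- NDplus-SC, 48 vs 24: SE = 14.70 × sqrt(1/48 + 1/24) = 3.67; half-width 7.20; power 76.6%.
- NDbasic-SC, 24 vs 24: SE = 14.70 × sqrt(1/24 + 1/24) = 4.24; half-width 8.32; power 63.6%.

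**The case against.** **The model may yet include phase.** The protocol allows further covariates at discretion, the full analysis set is not defined in the article, and the analysis plan is not shown. It would be wrong to assert that the final model will omit phase. But the covariate sentence gives baseline values as its example, while ADD/HD is fixed by name. A variable that sets the allocation probabilities should not be optional when a stratifying clinical factor is not. If phase II alone was meant, as the wording of the primary endpoint could suggest, Table 4 contradicts that.

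**The bias depends on an assumed d.** This stands. One eligibility table serves the whole study, the phase I sites are among the twelve, and the extra phase I procedures concern safety, laboratory values and imaging rather than the ODI. At d = 5 the biases are well inside the half-widths of 6.07 to 7.59. The documents show that the contrasts are exposed to a phase difference, not that one exists.

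**A reader might infer that the trial's power is materially overstated.** The arithmetic does not support this. With the phase term, the loss against the stated values is about 1, 2 and 0 points. The larger fall, from 71% to 64%, applies to NDbasic-SC only and arises only if phase I is set aside.

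**A reader might also infer that NDplus versus NDbasic really has 77% power,** the figure for 48 vs 24. It does not. Phase I randomised its 24 patients between exactly these two arms, so they belong in that contrast, and within-phase estimation keeps about 89%. Only the change of ratio needs adjusting for.

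**The abstract's ratio is not further evidence.** It carries the phase II ratio over to the whole trial. The Randomization section and Table 4 have the right totals, and the slip has no bearing on the model.

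**Conclusion.** The point holds as one about analysis. Of the patients counted against SC, 12 of 60 NDplus and 12 of 36 NDbasic could not have been assigned to SC. The stated model and Table 4 treat them as if they could. The two SC contrasts thus rest partly on non-concurrent, non-randomised comparisons. NDplus versus NDbasic is randomised in both phases and has only the smaller imbalance from 1:1 to 2:1.

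The size of any bias is conditional: 0.20d, 0.33d and -0.13d, with d assumed and taken as equal across arms. The gain from acting is the removal of this confounding; the correction to power is minor. Since the study is nonconfirmatory and centred on estimation, this should be fixed but does not undermine the trial. It still matters, because the estimates are meant to inform a confirmatory design.

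**What to change.** 1. Name phase (I/II) as a fixed factor in the ODI model, beside treatment and ADD/HD.
2. Report the two SC contrasts on phase II patients alone as a sensitivity analysis, with planning figures of 77% and half-width 7.20 (NDplus-SC, 48 vs 24) and 64% and 8.32 (NDbasic-SC, 24 vs 24). This checks the assumption in the main model that the phase effect is the same in every arm, which cannot be checked in SC.
3. Restate Table 4 with the phase-adjusted values: about 78% (NDplus-SC), 69% (NDbasic-SC) and 89% (NDplus-NDbasic), with half-widths 7.09, 7.93 and 6.14. Keep the phase I patients in NDplus versus NDbasic.
4. Separately, correct the abstract to 60:36:24 overall, with 2:1:1 for phase II only.

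The cost is one model term, one sensitivity analysis and a revised table. The largest loss of precision is in NDbasic-SC, where the half-width goes from 7.59 to 7.93 units. No additional patients are needed.
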